## Abstract

Background: Although mortality rates have declined in Uganda over the last decade, maternal mortality is still high at 336 deaths per 100,000 live births, as is infant mortality at 43 deaths per 1000 live births. One in every 19 babies born in Uganda does not live to celebrate their first birthday. Many of these deaths occur within the first 28 days of life, forming the single largest category of death. Promising effects for preventing death are expected from timed and targeted counselling (ttC), an intervention package of key messages and actions that address integrated health and nutrition needs of the mothers and children, barriers and negotiation agreement, to cause sustainable behavioural change at specific timelines in the first 1000 days. Methods: The study has a quasi-experimental design in order to evaluate the implementation and effectiveness of the ttC intervention. Participants are pregnant women who have been registered by village health team (VHT) members and who live in Hoima (intervention region) or Masindi (control region) districts, who will be monitored throughout their pregnancy up to at least six weeks after delivery. A multi-stage sampling technique will be employed to select participants, the study sites being purposively chosen. Sample size is determined using the pregnancy rate from the population estimates, resulting in a total required sample of 1218 (609 each in the intervention and control group). Study instruments that will be used include the Ugandan VHT household register (in which all mothers to be studied will be registered), the ttC register (an additional tool for the study area), and a study questionnaire, to collect data at outcome level. Univariate, bivariate and multivariate analyses will be performed using SPSS to evaluate intervention effects on outcomes (e.g., relationship between pregnancy outcomes and antenatal attendance). In addition, quantitative findings will be triangulated with qualitative data, and collected through interviews and focus group discussions with participants and implementers. Discussion: The proposed study will examine the effectiveness of implementing ttC to improve maternal and child outcomes in Uganda. If ttC is effective, broader implementation of appropriate antenatal services can be advised as essential newborn care improvements. Trial registration: PACTR, PACTR202002812123868. Registered on 25 February 2020.

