### 2.5. Conceptual Framework

The proposed study aims to determine the effect of ttC on pregnancy outcomes and newborn survival in rural Uganda. Specifically, the study aims to ascertain the extent to which ttC improves uptake of timely goal-oriented ANC with a focus on the recommended visits, and to determine whether ttC contributes to the recommended hygienic birth practices. Additional aims are to establish the extent to which ttC improves essential newborn care practices during the newborn period, and to ascertain the extent to which ttC fosters positive male involvement in pregnancy and newborn care. Finally, the study aims to ascertain the relationship between ttC implementation and appropriate pregnancy weight gain by end of pregnancy and appropriate birth weight.

We expect that if the VHTs implement ttC effectively, there will be an increased uptake of ANC services in the intervention districts, including the timely attendance of goal-oriented ANC services, and the development and implementation of a birth plan. In addition, we expect essential newborn care improvements at the levels of the health facility and the community, aimed at newborn survival within the first 28 days of life, as well as improved visible male involvement in MNH care, including escorting the pregnant women for at least one ANC where couple human immunodeficiency virus (HIV) counselling and testing occurs. Ultimately, we expect these improvements to result in appropriate pregnancy outcomes and newborn survival (see Figure 1).

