## 3. Data Management and Analysis

The data from the previous day of the study is entered and cleaned immediately, enabling immediate feedback on any issues to the data collection team. Once the team responsible for the tool returns from the field, brief conversations will be done to ensure that data was not missed at collection level.

Under the guidance of the statistician, a data entry template will be created using the expanded program of immunization info. All data shall be entered using this data entry template. Tools at data collection will be given a unique code. The process of unique coding will include sub-county, parish, village and then household number following the sampling frame. To ensure that each tool has a unique number, data collectors will be assigned numbers to use before heading into the field.

The data after entry is the responsibility of the statistician and the investigators at analysis. This data shall be attached to all publications for the world to have access to. This excludes personal data.

Univariate analysis will be done using SPSS, considering all data that requires a unilateral representation from the study. Baseline data as well as key demographic information from both comparison and implementation sites will be examined.

Several exploratory tests will be done to evaluate the data for dependencies and possible violations of normality and other key assumptions. Bivariate analysis will be used to determine the empirical relationship between study variables. This includes the differences between the implementation and comparison areas. In addition, the relation between the statuses at the baseline and the status of the indicators with a focus on the contribution of ttC will be examined. Next, multivariate analyses will be conducted, adjusting for potential relevant confounders (such as the implementation of a birth plan and a fourth ANC attendance (or more) on clean birthing practices). Depending on preliminary analyses, either fixed or random effects models will be selected for subsequent multivariate analysis, adjusting for the multi-level structure of the data, caused by the clustering of participants within villages.

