No	Variable	Description of Variable	Tool to Be Used
Dependent Variables			
1	Appropriate pregnancy weight gain at end of months pregnancy	Pregnancy weight gain of 11.5 kg to 16 kg by the end of the pregnancy	SQ
2	Newborn morbidity within the first 28 days of life	Newborn morbidity (focusing on cord infections, sepsis, asphyxia, fever, common flu and cold and diarrhea, pneumonia) within the first 28 days of life	SQ and ttCR
3	Appropriate birth weight	Appropriate birth weight of 2.5 kg or more	SQ
4	Mortality of newborns and mothers	If the mother died during pregnancy or childbirth, if the baby died either during pregnancy, childbirth or within the first 28 days of life.	SQ and ttCR
5	Overall maternal wellness	During pregnancy or newborn period, a mother does not develop sepsis, urinary tract infections, obstruction during birth or any danger signs during this period.	SQ and ttCR
Independent Variables			
1	Uptake of timely goal-oriented ANC	With a focus on the recommended four visits, the associated recommended services offered during these visits and timeliness of attendance.	VHTR, SQ and ttCR
2	Clean birthing practices	Birth attended by a skilled health provider, delivery happened in a health facility and a mama kit was used during the process.	SQ and ttCR
3	Essential newborn care practices (ENC) during the newborn period	Early initiation of breastfeeding, cord care practices, baby thermal care, sustained breastfeeding and baby WASH practices.	SQ and ttCR
4	Positive male involvement in pregnancy and newborn care	Man participates in at least one ANC, does an HIV test with the mother, available during birth, supports mother to help her rest, contributes finances for related logistics.	SQ

Notes: SQ: Study questionnaire, ttCR: ttC register, VHTR: Ugandan VHT household register.

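### Table 4 makes essential newborn care an independent variable for a mortality outcome that includes deaths before and at birth, so an association built on those roles can look protective when care has no effect

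*Protocol article*

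**What the plan says.** Table 4 (Study variables) divides the variables into dependent and independent.

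- Independent variable 3 is essential newborn care during the newborn period: "Early initiation of breastfeeding, cord care practices, baby thermal care, sustained breastfeeding and baby WASH practices". No time window or scoring rule is given.
- Dependent variable 4 is mortality of mothers and newborns. For the baby it asks "if the baby died either during pregnancy, childbirth or within the first 28 days of life".
- Dependent variable 2 is newborn morbidity to day 28, "focusing on cord infections, sepsis, asphyxia, fever, common flu and cold and diarrhea, pneumonia".
- All four independent variables are practices. Neither ttC nor district is among them. Newborn care and mortality are taken from the same two tools, the study questionnaire and the ttC register.

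Section 3 (Data Management and Analysis) states: "Bivariate analysis will be used to determine the empirical relationship between study variables". It adds that this covers differences between the two areas, and then moves to multivariate models. The Abstract, describing how intervention effects on outcomes will be evaluated, gives as its example the "relationship between pregnancy outcomes and antenatal attendance".

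Section 2.5 (Conceptual Framework) gives newborn care a different role. One aim is to "establish the extent to which ttC improves essential newborn care practices during the newborn period". The same section then states: "Ultimately, we expect these improvements to result in appropriate pregnancy outcomes and newborn survival".

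**The concern.** An independent variable should be settled before the outcome it is meant to explain. Here the order is reversed for the events that matter most. A baby who dies in pregnancy or during childbirth can receive none of the five practices. A baby who dies in the first hours cannot have had sustained breastfeeding and may have missed the others. For these babies the outcome determines the exposure.

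If they enter the analysis as not having received care, deaths pile up in the no-care group whatever care does. Adjustment for confounders does not cure this, and neither does a random effect for village, because the cause is time order and not confounding or clustering.

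Section 2.5 expects ttC to work through better practices, and the Abstract offers a practice–outcome association as an example of evaluating intervention effects. A spurious link between care and survival could therefore be read as support for ttC.

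**Working it through.** The plan gives no figure for this association, so there is none to reproduce. The check asks what such an analysis would show if care had no effect at all.

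**Inputs from the article**
- Neonatal mortality *m*: 19 per 1000 live births (Section 1, a global rate; no Ugandan neonatal rate is given).
- Coverage *c* among babies able to receive care: 65%, taken from the 35% of mothers said in Section 1 not to initiate breastfeeding. This is a stand-in for the whole set of practices.
- Participants: 1218 (Section 2.8).

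**Assumptions not in the article**
- Share *f* of neonatal deaths that occur before care can be given: 0.25 to 0.75.
- Stillbirths: 0, 10 or 20 per 1000.
- Babies who die before care is possible are scored as care not received.

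**Formulae, per 1000 live births, no stillbirths counted.** Early deaths *E* = *mf*; later deaths *L* = *m*(1 − *f*). Under no effect:
- risk with care = *cL* / [*c*(1000 − *E*)]
- risk without care = [*E* + (1 − *c*)*L*] / [1000 − *c*(1000 − *E*)]

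For *f* = 0.50, *E* = *L* = 9.5:
- With care: 0.65 × 9.5 = 6.175 deaths in 0.65 × 990.5 = 643.8 babies, 0.96%.
- Without care: 9.5 + 0.35 × 9.5 = 12.825 deaths in 356.2 babies, 3.60%.
- Risk ratio = 0.96 / 3.60 = 0.27, against a true value of 1.

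| Early share *f* | No stillbirths | 10 per 1000 | 20 per 1000 |
|---|---|---|---|
| 0.25 | 0.52 | 0.26 | 0.18 |
| 0.50 | 0.27 | 0.15 | 0.11 |
| 0.75 | 0.11 | 0.07 | 0.05 |

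At *f* = 0.50 without stillbirths, coverage of 30% to 98% gives 0.42 to 0.03. A second grid (mortality 20 to 30 per 1000, early share 33% to 67%, coverage 50% to 80%, no stillbirths) gives 0.10 to 0.51.

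**False positives.** In 2000 simulated trials per scenario (1218 births, 19 per 1000, 65% coverage, Fisher's exact test at two-sided 0.05, no true effect), the association was significant in 34% of trials at *f* = 0.25 and 85% at *f* = 0.50 without stillbirths. It was significant in over 99.9% at *f* = 0.50 with 10 or 20 stillbirths per 1000.

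**With a landmark.** Dropping babies who die before care is possible leaves, at *f* = 0.50, 6.175 / 643.8 with care and 3.325 / 346.7 without. Both are 0.96%, so the ratio is 1.00. Simulated rejection falls to 2.7% to 4.1%.

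**Morbidity.** Assume asphyxia in 2% to 5%, other illness in 10% to 30%, care in 0% to 30% of asphyxiated babies and in 65% of the rest. The spurious ratio runs from 0.46 to 0.94. The low end (5%, 10%, 0%) is 0.06175 / 0.6175 = 10.0% with care and 0.08325 / 0.3825 = 21.8% without. It requires that no asphyxiated baby receives care, so it is an extreme.

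**The case against.** The strongest reply is that the article writes out no model of newborn death or illness on newborn care. Its multivariate example in Section 3 concerns clean birthing practices, and the Abstract's concerns antenatal attendance. The bias also needs early deaths to be scored as no care. If they are left missing, the stillbirth and first-day part disappears. Scoring rules and risk sets commonly sit in an analysis plan, which is not shown. This reply limits what can be claimed: the size is conditional, and the absence of a scoring rule is not itself a fault. It does not remove the conflict between Table 4, which fixes newborn care as an explanatory variable, and Section 2.5, which treats it as something ttC changes.

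Three stronger readings are tempting and are not supported.

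- *That an asphyxiated baby cannot receive the care.* Asphyxia starts at birth and may delay breastfeeding, but nothing in the article shows that a surviving baby misses cord care, thermal care or hygiene practices. Most of the other listed illnesses can begin after care has started.
- *That any dataset would show strong protection.* At an early share of 0.25 without stillbirths, only 34% of simulated trials were significant. Practices analysed singly could also differ, since Table 4 does not say whether they are combined.
- *That the estimated effect of ttC is biased.* The end-term review is defined under Table 3 as a comparison of ttC and control areas. It does not use newborn care as a predictor.

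**Conclusion.** The point holds in limited form. Table 4's stated roles, followed literally through Section 3, lead to an association in which death can determine exposure, and those roles conflict with the aim in Section 2.5. If babies who die before care is possible are counted as not having received it, the illustrative risk ratio for death under no effect is about 0.1 to 0.5, and lower if the stillbirths that Table 4 includes are counted. That range rests on an assumed early-death share, an assumed scoring rule, an all-or-none care variable and a global mortality rate. For morbidity the bias is weak to moderate and comes mainly from asphyxia. The district comparison stands apart from this. The point is worth correcting because the change is small and the association could be misread as evidence for ttC.

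**What to change.** In Table 4, move essential newborn care from the independent variables to the outcomes (or label it a mediator) of ttC, in line with Section 2.5, and compare it by district among live births.

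If its relation to newborn death or illness is kept:
1. Set a fixed early landmark in advance, for example the end of day 1.
2. Include only babies alive and free of the event at that time.
3. Score only practices due by then.
4. Count only deaths or illnesses that start later.
5. Leave asphyxia out of this analysis.
6. Report the result as association, not as evidence of a ttC effect.

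Cost: a change to Table 4 and a few sentences in Section 3. Age at death and at illness onset must be recorded if they are not already; the questionnaire is not shown, and Section 2.11 still foresees pre-testing it. The landmark analysis also loses events. At 19 per 1000 live births, 1218 × 0.019 = 23.1 deaths are expected if all 1218 are live births. If half come before the landmark, about 11.6 remain, so the estimate would be imprecise.
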